## Discussion

3

In a recent systematic review and meta-analysis that assessed the effect of oral hygiene on periodontitis, it was found that there is a dose-response relationship in the conducts.^[22]^ In addition, regarding halitosis, a systematic review concluded that the use of toothbrushing plus tongue cleaning, when compared with toothbrushing alone, significantly reduced the indicators of halitosis. However, the authors suggested there is insufficient evidence to recommend frequency, duration and associated methods to tongue cleaning and that further research is needed to articulate a comprehensive clinical guideline.^[23]^ Furthermore, toothbrushing alone has not been found to be effective in reducing halitosis.

Therefore, we primarily expect to find that the regimen that will be followed by Group 1 is effective at removing biofilm from tooth surfaces, maintaining the oral health of the adolescents only using preventive oral hygiene methods. Thus, there is an additional gain in the form of reduced financial expenditures on professional dental services for the treatment of caries, with a consequent improvement in the quality of life of the volunteers.

Moreover, there has been a strong tendency toward the evaluation of patient-centered outcomes, modifying the old approach of focusing only on physiological aspects and the durability of a given product or treatment. As the literature offers no studies comparing the effectiveness of toothbrushes for the mechanical removal of dental biofilm with a concomitant investigation of acceptability and self-reported discomfort among adolescents, there is an evident need for studies that address these outcomes, since the combination of these factors is important to the satisfactory results of a product and/or treatment.

## Declarations

4

### Ethics committee

4.1

The Ethics Committee of *Universidade Metropolitana de Santos* approved this project under process number (33609920.4.0000.5509) in accordance with the guidelines of the National Ethics Committee. Any modifications to the protocol that may have an impact on the conduct of the study will be reported to this same committee. An informed consent form (which was approved by the Ethics Committee) will be signed by the caregivers and an assent form will be signed by participants, previous to their participation, by the researchers.

### Data collection methods

4.2

Researchers will be previously trained to collect data and perform the evaluations. All data will be entered electronically. The participants’ files will be stored in numerical order in a safe place, accessible only to the authors of this study.

### Discontinuing intervention

4.3

If volunteers choose not to continue, they can request to withdraw from the study, without any damage. These participants will be excluded from the study. All interventions and evaluations will be made at the same site, to make it easier for them to come, avoiding absences. No adverse effects are expected.

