#### Experimental groups

2.2.2

Patients will be divided into 2 groups (29 per group).

Group 1: will use a regimen with *Colgate Total 12* toothpastes + *Plax* mouthwashes + *Colgate Ultrasoft* toothbrushes (commercially available regimen);Group 2: will use *Colgate Cavity Protection* Toothpastes + *Colgate Ultrasoft* toothbrushes.

Volunteers will be instructed to use only their assigned products during the study period. These will be re-supplied at regular intervals. Volunteers will return with their assigned products to the study site before receiving new products.

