#### Sample calculation

2.2.3

The sample size was calculated to assure a test power greater than 95% and a significant level of α = 0.05. By using the data from Parizi et al,^[20]^ we estimated an effect size of 1.10. Figure 2 shows the plot of the test power as a function of the total sample size assuming normal data distribution, 2 tails and 2 independent groups.

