**Figure 2 F2:**
[figure not shown]
Shows that 23 subjects per group is sufficient to detect significant differences with a test power of 95%. Assuming a lost to follow up of 20%, 29 subjects are required in each group.

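### The rule that excludes withdrawn volunteers from the study, read naturally, takes randomised participants and their collected data out of the comparison, with a risk of bias whose direction is unsettled

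*Protocol article*

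**What the plan says.** Section 4.3 (Discontinuing intervention) lets volunteers withdraw on request and continues: "These participants will be excluded from the study". It does not say what happens to data they have already given.

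The sample size section and the Figure 2 caption plan for loss: "Assuming a lost to follow up of 20%, 29 subjects are required in each group". The evaluable target behind that is 23 per group.

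Section 2.7 schedules all variables, including the primary biofilm and gingival bleeding outcomes, at baseline and at 1, 3 and 6 months. Section 2.8 (Statistical analysis) names no analysis population, and section 4.2 (Data collection methods) does not say that data from withdrawn volunteers are kept.

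Under sections 2.2.2 and 2.4.4, Group 1 has a mouthwash, rinsed after brushing, and a different toothpaste. Group 2 has no rinse product. The blinding described in sections 2.4.2 and 2.4.4 is that of the examiners.

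**The concern.** The sentence in section 4.3 is a stated rule, not a detail left open. The sentence before it already has the volunteer leaving. If exclusion meant only that visits stop, it would add nothing, so a data manager following it literally would drop the participant. Someone who leaves after month 1 or month 3 has post-baseline plaque and bleeding scores that would go too.

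At stake is whether the groups compared are still the randomised groups. Participants can see which products they have, and one regimen has an extra step. Discomfort, satisfaction, side effects and complaints are themselves collected (section 2.5), and dissatisfied volunteers may be among those who leave. If leaving is related to both arm and outcome, a comparison without those who left is biased, and recruiting extra participants does not cure that.

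**Working it through.** **1. The plan's own figure.** Inputs from section 2.2.3: "we estimated an effect size of 1.10", "a significant level of α = 0.05", "assuming normal data distribution, 2 tails and 2 independent groups", and power of 95%.

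- Exact two-sample t test (noncentral t): 22.49, so 23 per group. Power at 23 is 95.4%.
- Inflation for 20% loss: 23 / (1 − 0.20) = 28.75, so 29 per group.

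Both figures reproduce, so the sample size is not in error. Retaining 80% of 29 leaves 29 × 0.80 = 23.2 per group. The allowance keeps power at its target after losses and says nothing about who is lost.

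**2. Bias when withdrawn participants are left out.** The document gives no rate by arm and no link between withdrawal and outcome, so the values here are assumptions. Let a fraction p of an arm leave, and let leavers score g SD worse than completers. With the arm's full mean set at 0 and the completers' mean at m:

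(1 − p)m + p(m − g) = 0, so m = p × g.

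If loss is related to outcome in one arm only, with p = 0.20:

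| g (SD) | Bias = 0.20 × g (SD) | Bias / 1.10 | Type I error, 23 per group |
|---|---|---|---|
| 0.25 | 0.05 | 4.5% | 5.3% |
| 0.5 | 0.10 | 9.1% | 6.3% |
| 1.0 | 0.20 | 18.2% | 10.2% |

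The type I error is that of a two-sided 5% t test with 44 degrees of freedom and noncentrality bias × √(23/2). Using 23 in both groups means that the other arm also loses about 20%, but unrelated to outcome.

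If loss is related to outcome in the same way in both arms, the bias is (p₁ − p₂) × g:

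- 20% and 20%: (0.20 − 0.20) × g = 0.
- 30% and 10%: 0.20 × g, again 0.05 to 0.20 SD. The sign reverses if the larger loss is in the other arm.

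**3. Extreme case.** If exactly the worst-scoring fraction p leaves one arm and nobody leaves the other, that arm's mean shifts by φ(z₁₋ₚ)/(1 − p): 0.195 SD at 10%, 0.350 SD at 20% and 0.497 SD at 30%. At 20% this is 0.20 × 29 = 5.8, about 6 people, and 0.350 / 1.10 = 0.32 of the planned effect.

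**4. Power if everyone is analysed as allocated.** With outcomes on all 29 per group, power at 1.10 is 98.4%. If keeping those who stop dilutes the effect (assumption), power is 95.9% at 10% dilution (1.10 × 0.90 = 0.99) and 90.9% at 20% dilution (1.10 × 0.80 = 0.88). Only the 20% case falls below 95%. Restoring 95% there would take about 35 per group.

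**The case against.** The strongest defence is that section 4.3 never mentions analysis. It stands among the declarations, beside the ethics text, and can be read as a rule about participation: no more products, no more visits. A reader might infer that the protocol expressly orders a completers-only analysis and deletion of earlier data. It does not say so. That limit stands, but it does not rescue the sentence, because on the participation reading it is redundant, and nothing else in the article keeps the data.

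Section 2.8's silence on analysis populations is not a fault here, since a full protocol or analysis plan may cover it. The point rests on the sentence that is written.

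Three further inferences go too far:

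- **That about 12 of 58 would be excluded under this rule.** 58 × 0.20 = 11.6, but the 20% is loss to follow-up, which is broader than voluntary withdrawal. The routine allowance from 23 to 29 also does not prove that a completers analysis is planned.
- **That anyone who stops the products is removed.** The text covers only volunteers who choose not to continue and ask to withdraw. A person who drops the mouthwash but keeps attending is not mentioned.
- **That the bias favours Group 1 because its regimen is heavier.** Withdrawal from the brushing-only arm is also possible.

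The plan does try to limit loss. Volunteers who have difficulty attending are not enrolled (section 2.2.1), motivation is repeated at return visits (section 2.4.1) and everything happens at one site (section 4.3). This may lower the number who leave. It does not settle how they are handled.

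**Conclusion.** The point holds as a risk created by a written rule. Read naturally, section 4.3 removes withdrawn participants and their collected outcomes from the comparison, and the article contains nothing that reverses this. Whether bias follows, and in which direction, depends on withdrawal patterns that the document does not give.

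Under the moderate assumptions the bias is 0.05 to 0.20 SD, small beside a planned effect of 1.10 SD but enough to raise the false-positive rate to about 10% at the upper end. The 0.35 SD figure is an extreme one-arm bound, not an expectation, and balanced loss that is equally related to outcome gives no bias. A reader might conclude that the primary comparison is certain to be biased, or that the trial is wrongly sized. The documents support neither. The sentence should still be changed, because the correction is nearly free and evaluations not sought from people who stop the products cannot be recovered later.

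**What to change.** Replace the exclusion sentence in section 4.3 with: *Participants who withdraw receive no further study procedures, but all data collected up to withdrawal of consent are kept, and all randomised participants are analysed in their allocated group; those who stop the products without withdrawing consent are invited to the remaining evaluations.*

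Analyse all available visits with a method that uses incomplete follow-up. A mixed model for repeated measures is one acceptable choice, not the only one. Report the completers-only comparison as a sensitivity analysis, and report withdrawals by arm, with timing and any reason given.

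The cost is a wording change, slightly more analysis work and possibly a slightly less favourable estimate. The sample size stays at 29 per group. If the sponsor expects dilution near 20% and wants to hold 95% power, the figure of about 35 per group is there to weigh, but the fix does not depend on it.
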